### Relevant Concomitant Care Permitted or Prohibited During the Trial

Adherence to interventions is crucial for scientific validity and participant well-being. The following strategies will be implemented to optimize adherence throughout the study: clear and comprehensive education during informed consent, and emphasizing the study’s purpose and the importance of adherence. Patients will be informed about the potential benefits, highlighting their contribution to advancing knowledge in lung cancer treatment. A multidisciplinary health care team, including surgeons, nurses, and support staff, will be involved in patient education and engagement. A collaborative approach ensures consistent information and support from various health care professionals. Treatment plans will be tailored to individual patient needs and preferences to enhance buy-in and motivation to adhere to the protocol. Patient-specific factors, such as lifestyle and cultural background, can improve adherence. Regular communication channels will be established between health care providers and participants to address concerns, provide ongoing support, and reinforce the importance of adherence. Telehealth or virtual platforms will be implemented for follow-up consultations to facilitate continuous communication. Patients will be included in decision-making to foster a sense of autonomy and ownership in the intervention process. Shared decision-making can enhance commitment and adherence to the chosen intervention. A robust monitoring system will be implemented to track participant progress and adherence. Timely feedback will be provided to participants on their progress. Acknowledgment of their contributions is considered positive reinforcement. Support programs, including psychological support and resources, will be offered to address the emotional and psychological aspects of the intervention. Support programs help patients to cope with challenges, fostering a positive attitude toward the intervention. Technologies, such as mobile apps and online platforms, will be adopted to provide educational materials, reminders, and real-time support. Technology can enhance engagement and facilitate communication between participants and health care providers. Flexibility will be offered in scheduling interventions to accommodate individual participant preferences and logistical considerations. Flexible scheduling can reduce barriers to adherence and increase overall participant satisfaction. Strategies will be implemented to maintain participant engagement, including newsletters, educational materials, and updates on study progress. This will ensure that participants feel connected and valued as contributors to the research endeavor.

### Provisions for Posttrial Care

The provisions for posttrial care in LUCENT are designed to ensure that participants receive appropriate medical attention and support even after their active involvement in the study has concluded. The posttrial care plan prioritizes the well-being of participants and addresses any ongoing medical needs that may arise. The key provisions for posttrial care include the following:

Continuity of standard medical care: Participants will continue to receive standard medical care for lung cancer as per established clinical guidelines, irrespective of their involvement in the study. The study team will facilitate the seamless transition of participants back to routine medical care provided by their health care providers.Access to study-related information: Participants will continue to have access to information related to the study, including summaries of study results, as they become available and appropriate for dissemination.Follow-up assessments: If any scheduled follow-up assessments or evaluations are part of the study protocol extending beyond the active trial period, participants will be informed about and encouraged to attend these follow-up appointments.AE monitoring: During the posttrial period, the study team will continue to monitor and address any AEs or complications related to the study interventions or procedures.Referral to specialists: If participants require specialized care or additional medical attention beyond the scope of the study, appropriate referrals to specialists will be facilitated.Communication and support: Participants will be provided with the contact information of the study team or a designated point of contact, allowing them to reach out with any questions or concerns about their participation or posttrial care.Emergency procedures: Clear procedures will be in place to manage any emergent medical situations that participants may face after the conclusion of the trial, with appropriate guidance on seeking urgent medical attention. The posttrial care provisions emphasize the ethical responsibility of the study team to prioritize participant welfare beyond the active study period. By providing ongoing support, access to information, and coordination with standard medical care, the study aims to ensure a comprehensive and ethical approach to the well-being of participants even after their active involvement in the observational study has ended.

### Ethical Considerations

The study protocol has received approval from ISMETT Palermo (IT) (IRRB/04/23 20/04/2023). All participants will provide informed consent before participating in the study. Participants will be informed that study findings may be published, and their confidentiality will be maintained.

## Results

### Outcomes

A comprehensive set of outcomes will be evaluated to gain insights into the clinical, psychosocial, and economic impacts of lung cancer treatment in Italy. The outcomes are categorized into primary and secondary objectives.

#### Primary Objectives

The primary objectives are as follows:

Performance assessment: (1) Development of national performance benchmarks based on the analysis of risk-adjusted outcomes and processes of care indicators; and (2) Evaluation of individual centers compared to national benchmarks for specific subgroups of patients.

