### Objectives

#### Primary Objectives

The project involves a web-based registry developed to facilitate data collection and evaluation of several different surgical, oncological, and socioeconomic outcomes of lung cancer patients diagnosed in early and locally advanced stages in Italy.

The primary objective is to generate data relevant to performance assessment through the development of national performance benchmarks based on the analysis of risk-adjusted outcomes and the processes of care indicators (eg, How does individual center X compare to the national standard in terms of length of stay for a certain subgroup of patients?).

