### Participant Timeline

Recruitment will be conducted from January 01, 2024, to December 31, 2026. Follow-up will be performed for a minimum of 2 years. The study will be completed in the year 2028. The assessments at baseline and follow-up are presented in Table 1.

**Table 1 table1:** Study assessments.

Assessment	Baseline	Follow-up
Visit month (from inclusion)	Yes	No
Informed consent	Yes	No
Check if patient meets the inclusion/exclusion criteria	Yes	No
Medical history	Yes	No
Physical examination, including weight	Yes	No
Hematology	Yes	No
Blood chemistry	Yes	No
Radiological assessment	Yes	No
Clinical variables	No	Yes
Health-related quality of life	Yes	Yes
Direct and indirect costs	Yes	Yes

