### Data Collection and Management

The plans for the assessment and collection of outcomes are as follows:

Longitudinal clinical outcomes: Regarding assessment, long-term clinical outcomes, including recurrence rates, overall survival, and disease-free survival, will be assessed through regular follow-up visits and medical records review. Regarding collection, outcome assessors will collect data during scheduled follow-up visits, and data entry personnel will ensure accurate and timely recording in the study database.PROs: Regarding assessment, patient-reported well-being and quality of life outcomes will be assessed using online questionnaires. Regarding collection, participants will be provided access to secure online questionnaire-completion platforms. Data will be automatically recorded in the study database.Health care resource utilization: Regarding assessment, health care resource utilization, including hospital stay and postoperative care, will be assessed through medical records and billing data. Regarding collection, data collection personnel will extract relevant information from medical records, and billing data will be obtained and recorded for economic analyses.Treatment decision patterns: Regarding assessment, patterns in treatment decisions, considering tumor characteristics and patient preferences, will be assessed through medical records and clinician interviews. Regarding collection, data collection personnel will document treatment decisions in the study database based on comprehensive reviews of medical records.Economic and psychosocial impact: Regarding assessment, economic and psychosocial impact assessments will be conducted through standardized tools and interviews. Regarding collection, trained personnel will administer economic and psychosocial assessments, and the results will be recorded in the study database.AEs and complications: Regarding assessment, continuous monitoring and medical records review will assess AEs and complications. Regarding collection, data collection personnel and safety monitoring teams will document AEs and complications in the study database.Stratification factors: Regarding assessment, stratification factors, including tumor stage and patient demographics, will be assessed at baseline. Regarding collection, data collection personnel will collect baseline information during participant enrollment and document it in the study database.Data quality assurance: Regarding assessment, regular audits and validation checks will continuously monitor data quality. Regarding collection, data management personnel will conduct routine quality checks to ensure the accuracy and completeness of the collected data.Data security and confidentiality: Regarding assessment, data security and confidentiality measures will be assessed through regular reviews and audits. Regarding collection, data management personnel will implement encryption, access controls, and other security measures to protect participant information.Reporting and analysis: Regarding assessment, reporting and analysis plans will be periodically reviewed and updated as needed. Regarding collection, the statistical team will conduct blinded data analyses to generate reports for internal and external stakeholders.

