### Statistical Methods

#### Statistical Methods for Primary and Secondary Outcomes

The demographic and baseline characteristics and follow-up outcomes will be described as mean, SD, median, and range for continuous variables, and percentage for categorical variables. Descriptive statistics will be calculated for the whole sample and by relevant subgroups (age, gender, diagnosis, etc). Statistically significant differences across groups will be detected using 1-way ANOVA. Multiple linear regression will be performed to investigate the impact of participant characteristics on short- and medium-term outcomes.

This study will use the official Italian EQ-5D-5L questionnaire to measure health and quality of life. The EQ-5D-5L descriptive system includes 5 dimensions: mobility (MO), self-care (SC), usual activities (UA), pain/discomfort (PD), and anxiety/depression (AD). Each dimension is articulated into 5 severity levels: no problems, slight problems, moderate problems, severe problems, and extreme problems (or unable to). Consequently, 3125 (55) possible health states are determined by response combinations and identified with a unique 5-digit number ranging from perfect health (“11111”) to the worst state (“55555”). Each health state will be converted into a single index value from 0 (assigned to death) to 1 (perfect health state), using predefined preference weights collected at the population level.

All statistical analyses will be performed using R software (R Project for Statistical Computing).

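### The primary objective is a risk-adjusted comparison of each centre with a national benchmark, but none of the methods stated for the primary outcomes produces that comparison

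*Protocol article*

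**What the plan says.** The protocol article states the primary objective twice. The Outcomes section lists "Development of national performance benchmarks based on the analysis of risk-adjusted outcomes and processes of care indicators" and then "Evaluation of individual centers compared to national benchmarks for specific subgroups of patients". The Objectives section of the Introduction illustrates the question: "How does individual center X compare to the national standard in terms of length of stay for a certain subgroup of patients".

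Statistical Methods for Primary and Secondary Outcomes then fixes three things:

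- Description: "Descriptive statistics will be calculated for the whole sample and by relevant subgroups (age, gender, diagnosis, etc" (the list is left open; centre is not named).
- Group comparison: "Statistically significant differences across groups will be detected using 1-way ANOVA".
- Modelling: "Multiple linear regression will be performed to investigate the impact of participant characteristics on short- and medium-term outcomes".

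Methods for Additional Analyses adds adjusted analyses by regression and stratification, with baseline features and comorbidity as confounders. Their declared purpose is to explore how treatment effects vary between patient subgroups. Centre does not appear.

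On baseline data, Table 1 has a row "Clinical variables" marked No at baseline and Yes at follow-up. Data Collection and Management says that "stratification factors, including tumor stage and patient demographics, will be assessed at baseline".

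**The concern.** The target quantity is, for each centre, the deviation of its outcome from a national value after allowing for its patient mix. A method that answers this must produce an estimate per centre, adjust it for case-mix, and define the national value it is set against. The methods written under the heading for primary outcomes do not combine these steps.

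The stake is the main product of the registry. The Conclusions of the abstract expect the benchmarks to guide clinicians and policymakers. An analysis that followed the stated methods faithfully would report differences between patient groups and the effects of patient characteristics, and would leave the centre question open. Patients treated in one centre also tend to resemble each other in outcomes such as length of stay, and the models as stated do not take this into account.

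**Working it through.** **Step 1: objective against method.** The target needs (a) a centre-specific estimate, (b) case-mix adjustment and (c) a national reference value.

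| Stated method | (a) Centre estimate | (b) Adjusted | (c) National reference |
|---|---|---|---|
| Descriptive statistics, whole sample and subgroups | only if centre is read into the open list | no | crude whole-sample value only |
| 1-way ANOVA | only if centre is taken as the group, and then as an omnibus test | no | no |
| Linear regression on participant characteristics | no; its coefficients belong to patient characteristics | yes, but with no centre effect to adjust | none defined |
| Additional adjusted analyses | centre not named; aimed at treatment effects | yes | none defined |

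No row meets all three. The section on nonadherence and missing data also mentions a primary analysis, but by treatment assignment, which is again not a centre comparison.

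**Step 2: clustering.** The Sample Size section states no target number, and the text gives no centre count, centre size or ICC. There is therefore no figure of the plan's own to reproduce. The values below are assumptions: ICC 0.01 to 0.10 and m = 20 to 100 patients per centre, with equal centre sizes and the participating centres regarded as a sample of centres.

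For a national mean or a centre-level contrast:

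- Design effect = 1 + (m − 1) × ICC.
- Factor by which the naive standard error is too small = √(design effect).
- True size of a nominal two-sided 5% test = 2 × [1 − Φ(1.96/√(design effect))].

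| ICC | m | Design effect | SE factor | True size |
|---|---|---|---|---|
| 0.01 | 20 | 1 + 19 × 0.01 = 1.19 | 1.09 | 7.2% |
| 0.05 | 50 | 1 + 49 × 0.05 = 3.45 | 1.86 | 29% |
| 0.10 | 100 | 1 + 99 × 0.10 = 10.9 | 3.30 | 55% |

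The regression actually stated concerns patient characteristics. If a share ρ of a characteristic's variance lies between centres, the design effect is about 1 + (m − 1) × ICC × ρ. At m = 50:

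- ρ = 0: 1.0 at any ICC, so no inflation.
- ρ = 0.2: 1 + 49 × 0.01 × 0.2 = 1.10 at ICC 0.01; 1.49 at ICC 0.05; 1.98 at ICC 0.10.

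**Step 3: baseline risk data.** Apart from the row "Clinical variables", Table 1 schedules history, physical examination, haematology, blood chemistry, imaging and quality of life at baseline. Data Collection and Management adds tumour stage and demographics. The material for risk adjustment is therefore largely planned; what is unclear is the meaning of one row.

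**The case against.** The best defence is that this is a condensed article. A full protocol is mentioned under the data-access plans, and an analysis plan may exist. Random effects, observed/expected ratios and robust standard errors are the sort of detail normally placed there. The subgroup list is open, adjusted regression is allowed, and the objective itself says risk-adjusted, so nothing rules out a centre effect.

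This stands for the detail: the article need not specify an estimator or a plotting convention. It does not stand for the mismatch. The article does fix methods under a heading that covers the primary outcomes, and those methods address a different question. An analysis plan that only elaborated them would still not reach the objective.

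Three stronger readings are tempting and are not supported:

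- A reader might infer from Table 1 that no clinical data are collected at baseline and that risk adjustment is therefore impossible. The other baseline rows, and the statement on tumour stage and demographics, contradict that. The undefined row may simply mean clinical outcomes.
- A reader might infer that the plan has decided to ignore clustering. It says nothing either way; the point follows only from the models as they are worded.
- A reader might take the larger error rates above as the error rates of this study. They apply to a test of a centre-level feature, which the document does not state, and every input is assumed.

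**Conclusion.** The concern holds as a mismatch between objective and method. The stated methods for the primary outcomes yield no case-mix-adjusted centre estimate against a national value, so the plan as written does not answer its primary question. This conclusion rests on the text alone and needs no assumption. Because it touches the primary objective, it should be corrected before analysis.

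The clustering part is secondary and conditional. Over the assumed range, standard errors of benchmark values and centre-level contrasts would be too small by a factor of 1.09 to 3.30. For patient characteristics that hardly vary between centres there is little or no effect. The true size for this study cannot be derived from the document.

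The Table 1 row is a point of clarity and is not the reason the objective goes unmet.

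**What to change.** Amend Statistical Methods for Primary and Secondary Outcomes to name the primary analysis. For each indicator, specify:

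- a model with a link suited to the type of outcome;
- prespecified baseline case-mix covariates;
- a centre effect, for example a random intercept by centre, or risk-standardised observed/expected ratios as an alternative;
- how the national value is defined, and the report of each centre's estimate with an interval against it;
- allowance for clustering by centre in the standard errors of benchmark and centre-level estimates.

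The choice between shrunken estimates and standardised ratios, the form of any funnel plot and any minimum volume for publication are matters of preference that the investigators can settle in the analysis plan.

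Separately, define the row "Clinical variables" in Table 1 and reconcile its baseline entry with Data Collection and Management and Methods for Additional Analyses, which rely on baseline tumour stage, demographics and comorbidity.

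The cost is protocol and analysis-plan wording and a clarification of one table row; no new visit is needed. The statistical price is that small centres receive wider or shrunken estimates.

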#### Secondary Objectives

The secondary objectives are as follows:

Economic impact assessment: Examination of the financial implications of innovative technologies or treatment pathways for lung cancer.Assessment of health care resource utilization for different surgical medical devices during a single episode of hospitalization.Psychosocial impact assessment: Investigation of the psychosocial impact of innovative technologies or treatment pathways, such as minimally invasive surgery.Assessment of PROs to determine the impact of new targeted treatments on quality of life.

#### Additional Outcomes and Considerations

The additional outcomes and considerations are as follows:

Longitudinal clinical outcomes: (1) Analysis of long-term clinical outcomes related to the chosen surgical interventions; and (2) Evaluation of recurrence rates, overall survival, and disease-free survival among participants.PROs: (1) Collection of PROs related to well-being, quality of life, and psychosocial factors; and (2) Utilization of online administration of questionnaires to enhance efficiency and data quality.Health care resource utilization: (1) Examination of the utilization of health care resources, including hospital stay, postoperative care, and associated costs; and (2) Identification of factors influencing resource utilization and potential areas for improvement.Treatment decision patterns: (1) Analysis of the patterns in treatment decisions, considering factors such as tumor characteristics and patient preferences; and (2) Exploration of the factors influencing the choice of surgical interventions.Patient characteristics and demographics: (1) Documentation of patient demographics, including age, gender, and other relevant characteristics; and (2) Analysis of how patient characteristics may influence treatment outcomes and decision-making.AEs and complications: Monitoring and documentation of AEs and complications related to the chosen interventions; and (2) Evaluation of the safety profile of different surgical modalities.

### Participant Timeline

Recruitment will be conducted from January 01, 2024, to December 31, 2026. Follow-up will be performed for a minimum of 2 years. The study will be completed in the year 2028. The assessments at baseline and follow-up are presented in Table 1.

**Table 1 table1:** Study assessments.

Assessment	Baseline	Follow-up
Visit month (from inclusion)	Yes	No
Informed consent	Yes	No
Check if patient meets the inclusion/exclusion criteria	Yes	No
Medical history	Yes	No
Physical examination, including weight	Yes	No
Hematology	Yes	No
Blood chemistry	Yes	No
Radiological assessment	Yes	No
Clinical variables	No	Yes
Health-related quality of life	Yes	Yes
Direct and indirect costs	Yes	Yes

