## Introduction

### Background and Rationale

Most lung cancer cases involve non-small cell lung cancer (NSCLC), while small cell cancer represents the minority of cases. To date, limited percentages of NSCLC cases are diagnosed in the early stage (in which patients are potential candidates for surgery, possibly followed by chemotherapy, to reduce the risk of recurrence) or in the locally advanced stage (in which the treatment is based on the use of chemotherapy, radiotherapy, and possibly, upon their completion, immunotherapy). The therapeutic strategy in patients with advanced NSCLC has changed in recent years. Until about 10 years ago, chemotherapy was the only option available; however, it was characterized by limited effectiveness. In recent years, the 2 crucial therapeutic “revolutions” we have witnessed in medical oncology (molecularly targeted drugs and then immunotherapy) have played essential roles in treating these patients. Some molecularly targeted drugs (primarily epidermal growth factor receptor [EGFR] inhibitors and then drugs directed against other molecular alterations) are superior to chemotherapy as a first-choice treatment, but the use of these drugs is limited to cases in which the tumor has those specific molecular alterations. Molecular analyses aimed at identifying these alterations in the tumor tissue represent a fundamental part of the diagnosis, which precedes the best treatment choice for each patient. In the next few years, we will probably see the continuation of those therapeutic “revolutions” mentioned above with the availability of new molecularly targeted drugs. These approaches will increase the therapeutic possibilities to be used in sequence after the failure of the approaches already available today [1]. Still, in some cases, they will allow a “targeted” treatment in the presence of molecular alterations for which no target drugs are available in clinical practice until now. Immunotherapy first established itself (about 5 years ago) as an effective treatment in patients who had already failed chemotherapy [1]. Subsequently, it was proven to be superior to chemotherapy as the first-choice treatment in cases characterized by high expression of the PD-L1 marker. Finally, significant results have been obtained in recent years by combining chemotherapy and immunotherapy, even in patients with low or absent PD-L1 expression. It is conceivable that in the coming years, based on a series of clinical trials recently conducted or still in progress, innovative drugs (targeted therapies and immunotherapy) will have essential roles in the treatment of early stages of cancer (used before surgery or after surgery) to reduce the risk of disease recurrence and hopefully increase the chances of recovery. The 5-year survival rate of lung cancer is low (16% in men and 23% in women), and it is at the bottom of the survival ranking, reminding us that, despite the critical progress made in recent years, there is a long way ahead regarding its treatment [2-4].

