### Trial Design

The Italian Lung Cancer Observational Study (LUCENT) is a prospective observational multicenter cohort study enrolling lung cancer patients who are candidates for minimally invasive manual, robot-assisted, or traditional open surgery. This study aims to investigate the outcomes of patients with early and locally advanced lung cancer in Italy. By using real-world data and patient registries, the study seeks to provide comprehensive insights into the clinical, psychosocial, and economic impacts of lung cancer treatment. The study’s observational nature allows for data collection in a naturalistic setting without intervention or manipulation by the researchers. The list of collaborating institutions has been provided in Multimedia Appendix 1.

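### Inclusion is the only visit clock named, so follow-up EQ-5D and costs compared by surgical approach can fall at different points of recovery

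*Protocol article*

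**What the plan says.** The Trial Design section describes a cohort "enrolling lung cancer patients who are candidates for minimally invasive manual, robot-assisted, or traditional open surgery". Under Intervention Description, the approach is chosen once eligibility has been assessed, on tumor characteristics, patient condition and the surgeon's expertise. Inclusion therefore normally comes before the operation.

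The only time origin in the article is in Table 1 (Participant Timeline), where the visit row reads "Visit month (from inclusion". The table has one baseline column and one follow-up column and lists no months. Health-related quality of life and direct and indirect costs are marked for both columns.

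The calendar in the same section reads "Recruitment will be conducted from January 01, 2024, to December 31, 2026", then "Follow-up will be performed for a minimum of 2 years. The study will be completed in the year 2028". The 2-year minimum is given without an origin.

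Several outcomes concern the operation. Additional Outcomes and Considerations lists "Analysis of long-term clinical outcomes related to the chosen surgical interventions", with recurrence, overall survival and disease-free survival, and also covers postoperative care, costs and safety by modality. The Secondary Objectives ask about the psychosocial impact of minimally invasive surgery. Explanation for the Choice of Comparators says that the surgical approaches will be compared. Other outcomes do not concern the operation, such as patient-reported outcomes under targeted treatments and patterns of treatment decisions.

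Statistical Methods for Primary and Secondary Outcomes names one-way ANOVA across groups and multiple linear regression on participant characteristics.

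**The concern.** A comparison of quality of life or cost between open, minimally invasive and robot-assisted surgery assumes that the groups are measured at comparable points after the operation. A visit counted from inclusion secures this only if the wait for surgery is about the same for everyone.

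The article gives no reason to expect that. It covers early and locally advanced disease. Background and Rationale considers it conceivable that newer drugs will gain a role in the "treatment of early stages of cancer (used before surgery or after surgery"). The only exclusion criterion is language, so a patient who has systemic therapy before the operation is eligible.

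The lag may also be related to the groups. Tumor characteristics and patient condition drive the choice of approach and could plausibly drive pre-operative therapy too, and centers may differ in their pathways. If so, the misalignment would bias the comparison as well as add noise. An assessment missed at the right point after surgery cannot be recovered at the analysis stage.

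**Working it through.** **Inputs from Participant Timeline.** Recruitment runs from January 1, 2024, to December 31, 2026, which is 1,096 days. Minimum follow-up is 2 years, origin not stated. Completion is in 2028, so December 31, 2028, at the latest. The visit clock is inclusion (Table 1).

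**Assumed input.** The lag L from inclusion to surgery is not given. It is taken as 30, 91 or 183 days (about 1, 3 and 6 months). The month-6 visit is an illustration, since the article lists no visit months.

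**Step 1: the plan's own calendar.** December 31, 2026, plus 2 years is December 31, 2028. The stated completion year is reproduced, with 0 days of slack, if the 2 years run from inclusion.

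**Step 2: recovery stage at a fixed visit.** Postoperative months = visit month − L / 30.4375. At month 6:

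| L (days) | Calculation | Postoperative months |
|---|---|---|
| 30 | 6 − 0.99 | 5.0 |
| 91 | 6 − 2.99 | 3.0 |
| 183 | 6 − 6.01 | about 0 |

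One visit label thus spans anything from the time of the operation to 5 months after it.

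**Step 3: whether the stated analysis allows for this.** The main methods section names ANOVA across groups and regression on participant characteristics. Methods for Additional Analyses adds adjustment for confounders such as baseline characteristics and comorbidities. Neither names time since surgery.

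**Step 4: postoperative follow-up of the last enrolled.** A patient included on December 31, 2026, has 24 months − L after surgery by the end of 2028. With uniform accrual and the same L for every patient, the share with less than 24 postoperative months is L / 1,096:

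| L (days) | Last patient, postoperative months | Share short of 24 months |
|---|---|---|
| 30 | 23.0 | 30/1,096 = 2.7% |
| 91 | 21.0 | 91/1,096 = 8.3% |
| 183 | 18.0 | 183/1,096 = 16.7% |

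The larger shares need every patient to have the long lag. With a mix assumed at 80% with 1 month and 20% with 4 months, over 36 months of accrual, the share is (0.8 × 1 + 0.2 × 4) / 36 = 1.6 / 36 = 4.4%.

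**The case against.** The strongest reply is that the article fixes no follow-up schedule at all. The Table 1 row is marked as done at baseline and not at follow-up, so it looks like a column label filled in as if it were an assessment. Visit timing is commonly left to the full protocol. Inclusion is also a sensible origin for a registry: eligibility rests on a lung cancer diagnosis, several outcomes have nothing to do with the operation, and a patient never operated on has no surgery date. Patients may also be included only after pre-operative therapy, which would make the lag short. All of this is fair. It limits how firmly the size can be stated, and it is why inclusion should stay as the origin for the whole cohort. It does not remove the point that inclusion is the only clock the article names, and that it does not suit comparisons by approach.

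Three stronger readings are tempting and are not supported:

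- **Immortal time in the survival comparison.** A reader might infer that recurrence and survival will be counted from inclusion, crediting operated patients with time before surgery. No section sets a survival time origin. The compared groups are all operated on, so pre-operative time biases a comparison between approaches only if it differs by approach, and nothing in the article shows that it does.
- **A distorted center benchmark.** The one example given for the primary objective is length of stay. Resource use in a single hospitalization and perioperative complications likewise belong to the hospital episode. None of these depends on the visit clock.
- **A calendar that fails.** A reader might infer that the 2-year minimum cannot be met within 2028. The article does not say that the 2 years run from inclusion, and it promises no 2-year postoperative endpoint. Counted from inclusion, the dates agree.

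**Conclusion.** The point holds as a cheap improvement. Follow-up EQ-5D and cost assessments compared by surgical approach are tied to no clock except inclusion, and the stated analysis does not account for time since surgery. Under assumed lags of 1 to 6 months, a month-6 assessment ranges from about 5 to about 0 postoperative months. This rests on the lag varying between patients, which eligibility allows but the article does not describe. Bias between approaches further requires that the lag differ by approach.

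The calendar is consistent. If the 2 years run from inclusion, the last-enrolled patients have somewhat less than 2 postoperative years at the end of 2028. That is ordinary administrative censoring of a small share when lags are short (2.7% at 30 days). It does not justify a later completion date or an earlier end of enrollment.

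**What to change.** In Participant Timeline and Table 1:

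1. Keep inclusion as the origin for describing the whole cohort and for outcomes not tied to surgery.
2. For outcomes compared by surgical approach, schedule the postoperative EQ-5D and cost questionnaires from the date of surgery.
3. Use the date of surgery as time zero for recurrence, disease-free survival and overall survival by approach, and report enrolled patients who were never operated on separately.
4. State the origin of the 2-year minimum. If it is inclusion, add that the last-enrolled patients will have slightly less than 2 postoperative years by the end of 2028 and are censored administratively. The completion date need not change.

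The cost is a short amendment, questionnaire triggers keyed to the surgery date, and two time origins to manage. The registry is already meant to collect perioperative details, so little extra data entry should be needed.
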